**Methods:**

The study is designed as a multi-center, randomized controlled trial. In total, an estimated number of *n* = 1,500 C&A with mental health problems, drawn from a school-based sample of *n* = 15,000 pupils attending school grades 6 to 13 (≥ 12 years of age), recruited in five regions of Germany, will be randomized either to an intervention (ProHEAD online) or a control condition. C&A in the intervention group will receive online access to tailored information and individual advice on where to seek professional help for their specific needs close to their place of living, case reports of and interaction with peers, as well as the opportunity for online and telephone counseling. C&A in the control intervention will receive a recommendation to seek help and online information on where to find professional help. All participants will be asked to complete questionnaires concerning their help-seeking behavior at baseline, during the intervention (monitoring), and also at a 1 and 2 year follow-up. The primary endpoint is the number of C&A seeking conventional face-to-face professional help in the real-world setting within 1 year after their initial screening.

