### Intervention

The intervention is individually delivered via the Internet. All C&A enrolled in this trial receive log-in information to an Internet-based platform that requires secured log-in. The web-based platform contains public content and a personal area with user-specific information and, depending on the group allocation, access to intervention modules. For participants in the control condition, the platform only contains information on the individual results of the school-based assessment and advice to seek professional counseling within the mental health care system. Moreover, the control group is granted access to addresses and names of local mental health care professionals and prompted by a static website encouraging them to seek help at the respective institutions. C&A in the control condition will only be contacted once and are not reminded or followed up outside of the school-based follow-up assessments. The design is justified by testing ProHEAD online against a real-world condition.

C&A allocated to ProHEAD online (intervention group) will receive their individual screening results, individual advice to seek professional help, and contact information for local mental health care professionals. Moreover, the intervention group is granted access to three additional modules: the *Information and Education Module*, the *Motivation and Guided Referral Module*, and the *Monitoring Module*.

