#### Monitoring Module

A monitoring system allows for the gathering of information regarding the help-seeking behavior of C&A in the intervention group. This will enable the case managers to tailor the intervention to a participants´ individual status, situation, and needs, allowing for adequate and tailored support of C&A. We distinguish automatized monitoring from individual monitoring. Automatized monitoring occurs based on user-website interaction in terms of 15 regular online assessments (Monitoring 1: 7 days after registration; Monitoring 2–7: every 14 days for the following 10 weeks; Monitoring 8–14: every 28 days for the following 32 weeks; Monitoring 15: 301 days after registration). As part of the automatized monitoring, C&A receive emails inviting them to complete a short questionnaire and motivating them to stay engaged with the platform. Automatized monitoring ends if C&A report successful help-seeking within the professional mental health care system. Alongside automated prompts, individual monitoring is realized via a team of case managers; each case manager tracks the progress of particular C&A. The case managers have different occupational backgrounds (e.g., psychologist, health education professional) and are trained in motivational interviewing [37] and all study-specific procedures (i.e., administration of the program). Individual monitoring includes individual communication (chat, phone, and email) regarding the progress and status on a regular basis. After registration participants will have access for up to 10 months. The dose of the intervention is primarily determined by the participating C&A. C&A are free to log in to the web-based platform according to their needs and interest. The system will send automated reminders to C&A who stay absent of the platform and have not made efforts to seek conventional face-to-face professional help.

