### Outcomes

The primary endpoint of the study is the 1-year follow-up, where all participants will be assessed on mental health problems and help-seeking intentions and behaviors, as well as actual help-seeking within the past year (primary outcome) in a second school-based assessment. A long-term follow-up will take place 2 years after the initial screening. C&A not participating at the school-based follow-up assessment will receive individual notices via email including a link to complete the assessment outside of the school environment if possible. All other medications and treatments used by participating C&A are permitted and will be assessed at the follow-up school-based screenings.

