### Statistical analysis

The main hypothesis is that a greater proportion of those C&A with mental health problems who are randomized to ProHEAD online (intention-to-treat) will present themselves within the conventional professional mental health care system after 1 year compared to C&A in the control condition. This will be addressed using chi-squared tests with Fisher’s exact *F* to adjust for zero inflation of cell distribution sizes (C&A who utilized professional help versus C&A who did not utilize professional help) on group differences. In secondary analyses, predictors of help-seeking behavior (i.e., sex, age, utilization of the online intervention, and symptom severity at initial school-based screening) will be assessed using multinomial logistic regression analyses. Engagement time per participant (minutes per day, days per month) and content of engagement will be tracked to get a reliable estimate of the utilization of the platform that is of interest for analyses of the dose-response relationship. Missing data and subjects withdrawn from the trial will be handled using an intention-to-treat approach. All subjects randomized will be considered in the analyses. In the case of drop-outs or missing data, it will be assumed that these C&A did not present themselves within the mental health care system to provide a conservative estimate of the true effect. Potential class and school effects will be tested and adjusted for if necessary.

In addition, a cost-effectiveness analysis, including the calculation of the incremental cost-effectiveness ratio (ICER), will be conducted. To provide information on cost per quality-adjusted life year (QALY), cost-utility analyses will be used.

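### Counting every missing pupil as not having sought help is called conservative, which holds only if 12-month retention is equal in both arms or lower in the intervention arm, and the protocol does not secure that

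*Protocol article*

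**What the plan says.** All points are in the protocol article.

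- **Analysis set and missing data (Statistical analysis).** "All subjects randomized will be considered in the analyses". For dropouts and missing data, the assumption is that "these C&A did not present themselves within the mental health care system to provide a conservative estimate of the true effect". This rule is fixed for the primary endpoint.
- **Control contact (Intervention).** "C&A in the control condition will only be contacted once and are not reminded or followed up outside of the school-based follow-up assessments".
- **Intervention contact (Monitoring Module; Motivation and Guided Referral Module).** "After registration participants will have access for up to 10 months". There are 15 automated online assessments, the last at day 301. Absent users get reminders, and case managers write to those who disengage.
- **Outcome collection (Outcomes).** Help-seeking over the past year is recorded for all participants in a school-based assessment. For those who miss it, "C&A not participating at the school-based follow-up assessment will receive individual notices via email including a link to complete the assessment". This sentence is not limited to one arm.

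The article gives no expected retention by arm and no control-arm help-seeking rate for the trial.

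**The concern.** A rule that turns every missing answer into a no is harmless to the comparison only when it removes help-seekers from both arms in equal proportion, and it is conservative when it removes more from the intervention arm. If it removes more from the control arm, it creates a difference in the hypothesised direction.

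The design gives a reason to ask. One arm is in contact with the study for most of the year, partly to keep pupils engaged. The other is approached once. If that contact makes intervention pupils even somewhat more likely to answer at 12 months, help-seeking by control pupils who do not answer goes unrecorded more often. The primary result would then partly reflect who responded, while the text assures readers that the bias can only run the other way.

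**Working it through.** **The plan's own figure.** The article has no retention figure to reproduce. The nearest benchmark is the detectable effect in Sample size: n = 1,500, a ratio of 1.13, also described as 13% differences, alpha 5%, two-sided. That power statement does not reproduce. The 5% critical value for a 2×2 table is 3.84, not 34.55, and 750 per arm gives about 30% power for a ratio of 1.13 from 25%. This is a separate matter. Only n, alpha and the 1.13 benchmark are used below.

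**Inputs**
- 750 per arm: 1,500 from the article, with 1:1 allocation assumed because the ratio is not stated.
- True help-seeking rate p, the same in both arms (no effect): assumed 25%, range 10% to 50%. The Background says about a quarter of affected adolescents receive treatment, but that is not a control rate for this trial.
- Retention r at 12 months: assumed 85% in the intervention arm, with gaps of 0 to 10 points below it in the control arm.
- Missingness assumed unrelated to outcome. If it is related, r should be read as retention among those who sought help.

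**Formula.** With missing coded as no, recorded rate = p × r in each arm. Under no effect, recorded ratio = r(intervention) / r(control), whatever p is.

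Rejection probability, with d the difference in recorded rates, p̄ their mean, SE0 = √(2p̄(1−p̄)/750) and SE1 the unpooled standard error:

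Φ((d − 1.96·SE0)/SE1) + Φ((−d − 1.96·SE0)/SE1)

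**Worked case, 85% vs 75%, p = 25%.** Recorded rates are 0.25 × 0.85 = 0.2125 and 0.25 × 0.75 = 0.1875, so d = 0.025 and p̄ = 0.20. SE0 = √(2 × 0.20 × 0.80/750) = 0.0207, and SE1 is the same to four decimals. The first term is Φ(−0.75) = 0.227 and the second 0.001. The total is 22.7%, nearly all favouring the intervention.

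**By retention gap, p = 25%**

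| Retention, intervention vs control | Recorded rates | Ratio | False-positive rate |
|---|---|---|---|
| 85% vs 85% | 21.25% vs 21.25% | 1.00 | 5.0% |
| 85% vs 83% | 21.25% vs 20.75% | 1.02 | 5.6% |
| 85% vs 80% | 21.25% vs 20.0% | 1.06 | 9.2% |
| 85% vs 75% | 21.25% vs 18.75% | 1.13 | 22.7% |

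**By true rate, 85% vs 75%.** 11.0% at p = 10%, 22.7% at 25%, 30.5% at 33%, 50.7% at 50%.

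**Cross-checks**
- At 90% vs 80% and p = 25% the formula gives 21.9%; a simulation with Fisher's exact test (20,000 runs) gives 19.9%.
- A complete-case analysis at the same retention, with missingness unrelated to outcome, stays at 5.0%.
- With equal retention of 80%, a true 25% vs 28.25% shrinks from 3.25 to 2.6 points, so the rule is then conservative for the difference.
- With retention reversed (75% intervention, 85% control, p = 25%), a false result favouring the intervention has probability 0.08%.

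**The case against.** The strongest reply is that the intensive contact concerns the online platform, whereas the outcome is collected elsewhere. Randomisation is individual, so both arms can sit in the same schools and be assessed on the same occasion, and attendance there does not depend on logging in. The e-mail fallback is not restricted by arm. Automated monitoring stops at day 301, or earlier once help-seeking is reported, and 15 questionnaires could tire pupils and lower intervention response. Small gaps do little: 2 points moves the error rate only from 5.0% to 5.6%.

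All of this stands, and it limits the point. A reader might infer that higher intervention retention is likely, or that a false benefit is to be expected. The documents do not support that; they leave the direction open.

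A reader might also take the Intervention and Outcomes sections to contradict each other over following up controls. They can be reconciled: the exception for school-based assessments may include the e-mail route to completing that same assessment. The wording needs clarifying, but is not a proven conflict. The abstract does have all participants monitored ("All participants will be asked to complete questionnaires concerning their help-seeking behavior at baseline, during the intervention (monitoring"), whereas the Monitoring Module says "A monitoring system allows for the gathering of information regarding the help-seeking behavior of C&A in the intervention group"; that is a minor correction with no bearing on the missing-data rule.

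Two further inferences fail. Pupils who have left school by month 12 fall in both arms and imply missingness, not a gap between arms. Nor is it shown that the rule understates uncertainty, since the test keeps its size when retention is equal.

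Sensitivity analyses may sit in a statistical analysis plan not shown, so their absence here is not the criticism. They would not make the unconditional claim true.

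**Conclusion.** The claim is wrong as written and should be fixed. The rule is conservative only under a condition that the protocol neither states nor secures, and it applies to the primary endpoint.

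The size depends wholly on assumed figures. With a true rate of 25%, 750 per arm and 85% intervention retention, the false-positive rate runs from 5.6% (2-point gap) through 9.2% (5 points) to 22.7% (10 points). For a 10-point gap it ranges from 11% at a true rate of 10% to 51% at 50%. The match with the stated detectable effect uses the ratio reading of 1.13; against 13 percentage points, the 2.5-point artefact at a 25% true rate would be small.

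Confidence is high in the conditional arithmetic. Whether a gap will occur, and in which direction, cannot be told from the document.

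**What to change.** 1. In Statistical analysis, delete the word conservative or state its condition: equal retention, or lower retention in the intervention arm.
2. Report 12-month missingness by arm.
3. Make the primary analysis one that is valid under missing at random, for example multiple imputation by arm using baseline help-seeking, GHSQ, SDQ and PHQ-A scores, sex, age and site. At the least, prespecify it as a key sensitivity analysis beside the missing-as-no rule.
4. Add a delta or tipping-point analysis that varies the help-seeking rate of non-responders separately in each arm.
5. Clarify the Intervention section against Outcomes, so that non-attenders in both arms get the same 12-month e-mail notices, in number and timing.

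The cost is revised wording, modest programming and one automated e-mail procedure common to both arms. The drawback is reliance on missing at random given baseline, itself untestable; the tipping-point analysis shows how far the conclusion depends on it.

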### Data monitoring and safety

All data will be collected via central servers that are used for both the school-based assessments and the intervention conducted via the ProHEAD platform (www.prohead.de). All study data will be stored under a code, ensuring complete pseudonymization. Computerized assessments guarantee the highest level of data integrity and quality; i.e., missing data will be minimized, and false data entry will be prevented. Online access allows for continuous monitoring of data collection, documentation of access logs, and traceability of all entered data (user and timestamp) as well as restoration of all previous states. A Distributed Replicated Block Device (DRBD)-based cluster will provide synchronous replication of all data during data entry on two separate servers, as well as highest availability. In addition, full and incremental backups will be conducted following a predefined backup plan.

Data will be handled in accordance with German legal regulations concerning data protection and data security (Landesdatenschutzgesetz Baden-Württemberg and Bundesdatenschutzgesetz) as well as European Union (EU) General Data Protection Regulation. Data storage and transfer will be encrypted. Access to the data will be strictly limited to authorized persons and will be password-protected. All servers are located at the University Hospital Heidelberg. Data will be stored for at least 10 years at the primary research institution. The data will be accessible for project partners and their respective statistical experts.

Monitoring will be done according to the Guidelines for Good Clinical Practice (ICH-GCP). The Coordination Center for Clinical Trials (KKS) Heidelberg will oversee the study procedures at all five recruiting centers. In particular, the recruitment of schools and the students within these schools will be monitored in order to obtain adherence to the study manual and documentation guidelines and to ensure equivalent procedures at all sites.

An independent Data and Safety Monitoring Committee (DSMC) is formed by PD Dr. phil. [name] (University of Tübingen), [name]. rer. nat. [name] (University Hospital Aachen), and [name]. med. [name] (University of Zurich). The DSMC will oversee all aspects of data collection, handling, and analysis.

### Stopping rules

Stopping rules for C&A participating in the trial are the reporting of acute suicide plans or suicide attempts while participating in the ProHEAD intervention, as communicated with the case manager. In case of the reporting of acute suicide plans or attempts, special emergency procedures will be put in place that allow immediate contact with the participant in order to assess risks and refer to appropriate care. The case manager will try to get the participant to immediately seek help via an ambulance or the police. If no commitment can be achieved for voluntary help-seeking, the case managers will ascertain the first name and surname of the participant to report the plans to the local police. Further, C&A who withdraw consent to participate in the trial will discontinue participation. There are no discontinuation criteria for the whole trial.

### Ethical issues

The study will be conducted in accordance with the Declaration of Helsinki and the regulations for physicians of the medical association (Landesärztekammer) of Baden-Württemberg in their currently valid version. Study participation is voluntary. A participant can withdraw consent at any time without stating the reason and without any individual disadvantage for subsequent medical care. Study participants and their parents or alternatively persons with parental authority will be informed in writing about the procedures and potential undesirable effects or risks of the study. Their approval will be documented via their signature on the informed consent forms. The Ethics Committee of the Medical Faculty at the University of Heidelberg will be informed in case of severe adverse events or other unintended effects of the trial interventions.

### Dissemination of results

In addition to research publications and conference contributions, the ProHEAD Consortium will take several measures to disseminate the results beyond the scientific community. Information about the project and the availability of the Internet-based interventions and e-mental health tools (after-study stage) will be provided to patients and health care providers as well as to youth organizations and schools. Awareness in the general public will be increased by the ProHEAD website (www.prohead.de) and press campaigns accompanying the development of the project, disseminating its results.

## Discussion

The aim of the trial is to investigate if an Internet-based intervention can increase help-seeking behavior in C&A with mental health problems. Existing empirical research suggests that e-interventions are indeed capable of promoting help-seeking behavior in youths [38, 39]. Most C&A prefer technology-based interventions over a face-to-face in-person contact [40]. Internet-based mental health services offer anonymous help in an unobtrusive but easily accessible way that is modern and age-appropriate. In this manner, C&A in need can be reached who otherwise would not find their way into the health care system, e.g., because of stigma, fear, or structural reasons. However, some interventions based on e-technology previously implemented failed to help participants to ask for professional help [41, 42]. A systematic review analyzed 18 studies investigating the effects of e-interventions on young people’s help-seeking and identified a number of shortcomings in existing studies [20]. According to this review, some trials showed no methodological rigor (e.g., a lack of control group, no follow-up assessments) or included participants with mild mental health problems only. Furthermore, the majority of programs placed an emphasis on information only, did not include interactive modules, and were evaluated in small community-based samples. Using a randomized controlled design on a large-scale sample, the present study aims to overcome these shortcomings. The intervention is suitable for a broad range of C&A affected by different mental health problems with clinical relevance. At the same time, a unique strength of the intervention is the individual mentoring, enabling customized support for each participant. Cooperation with consortium partners all over Germany allows for the recruitment of a representative sample of *n* = 15,000 C&A, of which *n* = 1,500 (10%) are expected to fulfill eligibility criteria for the present trial. The consortium members have long-standing experience in school-based recruitment and mental health assessment of C&A [43–45]. The school-based screening reaches all C&A without self-selection bias and enables an intention-to-treat approach.

Despite the significant advantages of a large scale multi-center study, running a trial in different study centers comes with special demands. There is a risk that single study sites may perform differently in recruitment, placing a requirement for special attention on standardized study implementation. For this purpose, a special training for recruiting staff from all study sites will take place prior to the baseline screening to ensure strict adherence to the study manual. Standardized information material further supports comparable results and reduces study site-specific biases. Participation in the study does not present any obvious risks for C&A. All participants, including those in the control condition, will receive information on where to seek help for mental health problems.

### Implications and future impact

Young people are familiar with the Internet and online programs. They can access them at any time in accordance with their individual needs. Therefore, an online intervention might be the superior way to provide tailored information and low-threshold access to enhance help-seeking for mental health problems among youths.

Especially in this population, interventions are needed, because early detection increases the chance of early treatment. This diminishes the risk of recurrence and/or serious residual damage, thereby providing an opportunity to improve psychosocial outcomes and reduce health economic costs [12, 13].

If the intervention is shown to be effective, the present study has the potential to narrow the treatment gap in C&A and to ultimately improve the mental health care system.

